# Cost-effectiveness of immediate versus delayed sequential bilateral cataract surgery in the Netherlands (the BICAT-NL study): study design of a prospective multicenter randomised controlled trial

**DOI:** 10.1186/s12886-020-01521-x

**Published:** 2020-06-29

**Keywords:** Immediately sequential bilateral cataract surgery (ISBCS), Delayed sequential bilateral cataract surgery (DSBCS), Randomized controlled trial, Cost-effectiveness, Refraction, Complications, Visual acuity, Patient reported outcome measures (PROMs)

## Abstract

**Background:**

Cataract surgery is one of the most frequently performed types of surgery. Most patients suffer from bilateral cataract and while cataract surgery of only one eye is effective in restoring functional vision, second-eye surgery leads to further improvements in health-related quality of life, and is cost-effective. At present, most patients undergo cataract surgery in both eyes on separate days as recommended in national guidelines, referred to as delayed sequential bilateral cataract surgery (DSBCS). An alternative procedure involves operating both eyes on the same day, but as separate procedures, known as immediately sequential bilateral cataract surgery (ISBCS). The aim of this study is to evaluate the effectiveness and costs of ISBCS compared to DSBCS, in order to test the hypothesis that ISBCS is non-inferior to DSBCS in terms of effectiveness and superior to ISBCS in terms of cost-effectiveness.

**Methods/design:**

Multicenter non-inferiority randomised controlled clinical trial. Patients (18 years or older) with bilateral cataract and an indication for bilateral cataract surgery with an expected uncomplicated intraoperative and postoperative course are included in the study. Patients are randomly assigned to either ISBCS or DSBCS. The primary endpoint is the proportion of patients with a refractive outcome in the second eye within 1.0 dioptre from the target refraction, at 4 weeks after surgery. Secondary outcomes include corrected and uncorrected distance visual acuity, complications, patient reported outcomes (PROMs), cost-effectiveness, and budget impact. Follow-up visits are planned at 1 week after first-eye surgery and 4 weeks after second-eye surgery. At 3 months after first-eye surgery, the occurrence of complications is checked and patients fill in a final questionnaire.

**Discussion:**

This study protocol describes the design of a multicenter non-inferiority randomised controlled trial. Current studies on ISBCS often lack information on safety regarding refractive outcomes. In addition, there is a lack of well-designed cost-effectiveness studies using established methods. The BICAT-NL study will provide more insight in refractive and cost-effectiveness outcomes for ISBCS compared to DSBCS.

**Trial registration:**

This study was prospectively registered at Clinicaltrials.gov on January 17th 2018. (Identifier: NCT03400124.

## Background

Cataract surgery is one of the most frequently performed types of surgery in the world. In the Netherlands, the current estimated number of cataract extractions is over 180,000 per year [1, 2]. This number has increased rapidly over the years. As a result, national healthcare expenditures on cataract have increased as well. Due to the vast number of cataract patients, small efficiency gains in cataract care delivery may lead to substantial cost savings on a macro level.

The majority of patients, mostly elderly, suffer from bilateral cataract. A previous study showed that 71% of patients with cataract had an indication for bilateral surgery [3]. While cataract surgery of only one eye is effective in restoring functional vision, studies have shown that cataract surgery of the second eye leads to further improvements in health-related quality of life, and is cost-effective [4–6].

At present, most patients undergo cataract surgery in both eyes on separate days, as advised in the Cataract guidelines of the Dutch Ophthalmology Society, with a delay of at least 2 weeks (delayed sequential bilateral cataract surgery, DSBCS) [7]. However, over the past years some have argued that the procedure is now safe enough to perform in both eyes on the same day during a single operating session (immediately sequential bilateral cataract surgery, ISBCS) [8]. These advocates substantiate their attitudes to ISBCS through the many advances in the field of cataract surgery and consider ISBCS to be safe when risks of complications related to surgical procedures are minimized [9].

The two primary reasons for delaying second-eye surgery are the risk of bilateral endophthalmitis and the risk of refractive surprise. Endophthalmitis is most likely to occur within the first 2 weeks after surgery. When this happens, cataract surgeons may decide to abstain from second-eye surgery. However, unilateral endophthalmitis is a rare complication, especially since the introduction of intracameral antibiotic prophylaxis. Several retrospective and epidemiologic studies have reported that the administration of intracameral antibiotics significantly reduces the risk for developing endophthalmitis compared to other prophylactic measures, such as topical antibiotics [10, 11]. More recent studies on incidences of endophthalmitis after administration of intracameral antibiotics, show endophthalmitis rates of 0.039% (Spain) [12] and 0.029% (Sweden) [13]. In addition, the study on Swedish national data reports a significant decrease in endophthalmitis rates compared to previous years [13]. The calculated probability of endophthalmitis occurring bilaterally is extremely low (1: 70 million cases) [8]. So far, the few cases of bilateral endophthalmitis after ISBCS that have been described could be attributed to faults in aseptic procedures [14]. Three randomised controlled trials (RCTs) [15–17] and several non-comparative studies [18–26] found no significant differences in (severe) complication rates. With regard to refractive outcomes, delaying second-eye surgery enables cataract surgeons to evaluate the outcomes of the first eye and, if necessary, adjust their plans for second-eye surgery [27]. In the Netherlands, the standard for success that is used in cataract surgery is a postoperative refraction within 1.0 diopter of the target refraction [28]. Only two previous studies, one randomised study and one nonrandomised comparative study, [15, 29] report data on refractive outcomes for ISBCS compared to DSBCS. These studies showed similar refractive outcomes for ISBCS compared to DSBCS, indicating that refractive surprises may be prevented with careful patient selection [15, 25, 29, 30]. However, the number of patients in these two studies was limited and the overall quality of the evidence of the RCT was graded low to moderate [31]. Therefore, concerns remain with regard to refractive outcomes.

Furthermore, available studies on cost analyses showed that ISBCS resulted in fewer costs and important cost savings to third-party payers, patients, and society compared to DSBCS [3, 32–36]. However, to date, only one (model-based) cost-utility analysis has been performed [36].

Therefore, the aim of the BICAT-NL (Bilateral Cataract surgery in the Netherlands) study is to evaluate the effectiveness and costs of ISBCS compared to DSBCS in the Netherlands in order to test the hypotheses that ISBCS is non-inferior to DSBCS in terms of effectiveness and superior to ISBCS in terms of cost-effectiveness.

## Methods/design

### Objectives

The primary objective of this study is to evaluate whether ISBCS is non-inferior to DSBCS regarding effectiveness, where effectiveness is defined as the proportion of patients with a postoperative refraction that deviates ≤1 D from target refraction. Secondary objectives of this study are to evaluate ISBCS versus DSBCS regarding non-inferiority of (1) the proportion of patients with a postoperative refraction within 0.5 D of target refraction, and (2) postoperative visual acuity, and superiority of (3) patient satisfaction (using patient reported outcome measures (PROMs)), (4) the incidence of complications, and (5) cost-effectiveness.

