### Outcome measures

The primary outcome is the proportion of patients in both treatment groups with a postoperative refraction in the second eye that deviates ≤1.0 D from target refraction 4 weeks after cataract surgery of the second eye. This is an accepted norm to define success in terms of refractive outcomes after cataract surgery [7, 28].

Secondary outcomes will include:
**Refraction**: the proportion of patients in both treatment groups with a postoperative refraction in the second eye that deviates ≤0.5 D from target refraction 4 weeks after cataract surgery of the second eye.**Visual acuity**: ETDRS, uncorrected and corrected distance visual acuity in LogMAR (the Logarithm of the Minimum Angle of Resolution), 1 week after first-eye surgery and 4 weeks after second-eye surgery, corrected for baseline visual acuity. In addition, the proportion of patients with a final corrected distance visual acuity (CDVA) of ≤0.1 LogMAR (measured at 4 weeks after second-eye surgery) will be compared for ISBCS and DSBCS.**Complications**: the number of intraoperative and postoperative complications within 3 months after first-eye surgery.**Patient-reported outcome measures (PROMs)**, including patient satisfaction, vision-specific quality of life, and health-related quality of life:

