### Statistical analysis

All data will be collected in a database (Castor) and will be exported to IBM SPSS Statistics (IBM, Armonk, NY, USA) for data analysis. The data analyses will be performed according to the intention to treat principle. However, considering that second-eye surgery can be delayed in ISBCS patients with complications during first-eye surgery, the analyses will be repeated based on a per protocol analysis. As recommended for non-inferiority trials in literature, both analyses will be performed and non-inferiority will be established if both analyses produce the same conclusion [42]. For all analyses, stratification variables (center and axial length) are accounted for by including them in the analysis model and significance levels will be set at 0.05.

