#### Secondary outcomes

For secondary outcomes, data analyses will be performed as follows: presence of non-inferiority of ISBCS compared to DSBCS regarding the difference in the proportion of second eyes with a refractive outcome within ±0.5 D of target refraction will be evaluated similar to the method described under primary outcome. For visual acuity, presence of non-inferiority of ISBCS will be evaluated by comparing the proportion of patients with a corrected distance visual acuity (CDVA) 4 weeks after surgery of the second eye of ≤0.10 LogMAR between groups. The computed sample size of 858 patients for the primary outcome translates to an allowed non-inferiority margin of 10% to establish non-inferiority at the 0.05 alpha level regarding this secondary outcome measure. Corrected and uncorrected distance visual acuity in second eyes, patient-reported outcomes, and utilities will be analysed using a linear mixed model to test for overall differences between groups over time. The difference in the incidence of intraoperative and postoperative complications will be analysed using mixed-effects logistic regression to account for the fact that both eyes of each patient are included in the analysis and nesting of patients within centers.

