## Discussion

Worldwide, an increasing number of cataract surgeries is performed over the years and healthcare expenditures are rising. Therefore, small efficiency gains in cataract care delivery, such as those potentially gained in ISBCS, may lead to substantial cost savings on a macro level. ISBCS is increasingly practiced on a routine basis in a number of countries around the world, including Finland, certain regions in Spain, and Canada [47]. Potential benefits of ISBCS include less time between surgeries, fewer hospital visits, a faster total recovery period due to simultaneous postoperative care (eye drops) in both eyes and less use of homecare. As a consequence of the recent COVID-19 crisis we now face a scenario where the number of hospital visits, if feasible, should be decreased to diminish the risk for contamination in the hospital. ISBCS could be an instrument to significantly decrease residence time of patients in the clinic for surgery as well as for postoperative controls. However, opponents of ISBCS argue that the potential risks of severe bilateral complications and unexpected refractive outcomes supersede any economic arguments [48]. The main concerns about ISBCS include potential risks of bilateral complications of cataract surgery, most importantly the very rare but severe risk of endophthalmitis and the risk of refractive surprise (a significant deviation from the predicted refraction).

Further investigation is required to evaluate how ISBCS compares to DSBCS with respect to cataract surgery outcomes, in particular with regard to refractive outcomes. In addition, there is a lack of well-designed cost-effectiveness studies using standard methods. The BICAT-NL study will provide more insight in refractive and cost-effectiveness outcomes for ISBCS compared to DSBCS.

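### Complications are listed as a superiority objective for ISBCS, although the protocol's stated worry is that ISBCS might be worse; failing to show superiority would not support a claim of no excess harm

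*Protocol article*

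**What the plan says.** The Objectives section assigns a hypothesis type to each secondary objective. Refraction within 0.5 D and visual acuity are to be tested for non-inferiority. The remaining three are to be tested for "superiority of (3) patient satisfaction (using patient reported outcome measures (PROMs)), (4) the incidence of complications, and (5) cost-effectiveness".

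The rationale for complications points the other way. The Background states: "The two primary reasons for delaying second-eye surgery are the risk of bilateral endophthalmitis and the risk of refractive surprise". The Discussion adds that "The main concerns about ISBCS include potential risks of bilateral complications of cataract surgery", and that "opponents of ISBCS argue that the potential risks of severe bilateral complications and unexpected refractive outcomes supersede any economic arguments".

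The outcome is defined under Outcome measures as "the number of intraoperative and postoperative complications within 3 months after first-eye surgery". Under Secondary outcomes the analysis is given as follows: "The difference in the incidence of intraoperative and postoperative complications will be analysed using mixed-effects logistic regression", with both eyes included and patients nested in centers. Statistical analysis adds that "significance levels will be set at 0.05". No margin, direction or target effect is given for complications, whereas a 10% margin is given for corrected visual acuity in the same section.

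**The concern.** A superiority objective asks whether ISBCS causes fewer complications. The protocol's safety question is whether it causes more. The potential benefits of ISBCS listed in the Discussion concern the interval between operations, hospital visits, recovery and home care; fewer complications are not among them. Both arms use a standard phacoemulsification technique and receive intracameral antibiotics, so the article offers no mechanism for a lower rate.

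The other main worry, refractive surprise, is correctly put as non-inferiority. For complications, a non-significant result would establish neither that ISBCS is better nor that it is no worse. The Background says that earlier trials and series "found no significant differences in (severe) complication rates"; a failed superiority test would add one more statement of that kind. What is at stake is the conclusion that the trial can draw on a safety concern that its own Discussion calls a main one.

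**Working it through.** **Inputs from the protocol article.** 386 patients per group, 772 in total, 858 with 10% loss; one-sided alpha 0.05 and 90% power for the primary endpoint; 94% expected in both arms; margin 5 points (Sample size calculation, Primary outcome). Endophthalmitis rates of 0.039% and 0.029% (Background). No other complication rate is given.

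**The plan's own figure.** n = 2 × 0.94 × 0.06 × (1.645 + 1.282)² / 0.05² = 386.4 per group, stated as 386. Then 772 / 0.90 = 857.8, stated as 858. The sample size is reproduced, and it was set for refraction only.

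**Assumptions for complications.** Eye-level rates p of 2%, 5% and 10%; within-patient correlation 0.2. Two eyes per patient give 386 × 2 = 772 eyes per arm and a design effect of 1 + 0.2 = 1.2, so n = 772 / 1.2 = 643 effective eyes.

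**What a null result would leave open.** With equal observed rates:

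- half-width of the 95% CI for the difference = 1.96 × √(2p(1 − p)/n)
- upper 95% limit of the risk ratio = exp[1.96 × √(2(1 − p)/(np))]

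At p = 5% these are 1.96 × √(0.095/643) = 2.4 points and exp[1.96 × √(1.90/32.15)] = 1.6.

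**Power, two-sided 0.05.** Power = Φ(|p₁ − p₂| / √[(p₁(1 − p₁) + p₂(1 − p₂))/n] − 1.96). For a doubling from 5% to 10%: 0.05 / √(0.1375/643) = 3.42, and Φ(1.46) = 93%.

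| Assumed rate | CI half-width (points) | Upper limit, risk ratio | Power, 25% fewer | Power, 50% fewer | Power, doubling |
|---|---|---|---|---|---|
| 2% | 1.5 | 2.1 | 10% | 31% | 56% |
| 5% | 2.4 | 1.6 | 19% | 66% | 93% |
| 10% | 3.3 | 1.4 | about 36% | 93% | over 99% |

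**Sensitivity to the correlation.** With independent eyes (n = 772) the upper risk-ratio limits are 2.0, 1.5 and 1.4. With complete correlation (n = 386) they are 2.7, 1.9 and 1.5.

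**Endophthalmitis at the quoted rates.** Expected cases per arm: 772 × 0.00029 = 0.22 to 772 × 0.00039 = 0.30. Chance of no case in either arm (1,544 eyes): 64% to 55%. No event in 772 eyes gives a one-sided 95% upper limit of 1 − 0.05^(1/772) = 0.39%, about 10 to 13 times the quoted rates.

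**Would formal non-inferiority be feasible?** At patient level, with 386 per arm, one-sided 0.05 and equal true rates of 2%, 5% and 10%, power = Φ(margin / √(2p(1 − p)/386) − 1.645). An illustrative 2-point margin gives 63%, 36% and 24%. A 5-point margin gives over 99%, 94% and 75%.

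**The case against.** The strongest reply is that the Secondary outcomes section, not the list of objectives, governs the analysis, and there the test is of a difference with no direction. One-sided testing is specified for the primary outcome and carried over only to the 0.5 D outcome. If the complication test is two-sided, it can detect harm: the last column of the table shows good power for a doubling at rates of 5% and 10%. The model also yields an estimate and an interval. This stands. A reader might infer that the trial cannot speak to safety at all, and the document does not support that.

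A reader might also infer that a null result will be reported as no difference. No section sets such a rule; the Background phrase describes earlier studies.

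Further, the decision model in the Cost-effectiveness analysis section is meant to take in rare bilateral events. It does so for the economic evaluation only, so it tempers the point without replacing a safety objective. The Background also calls the calculated probability of bilateral endophthalmitis extremely low and ends on refractive outcomes, which are the powered endpoint. That is fair, but the Discussion still names bilateral complications among the main concerns.

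Finally, the 2%, 5% and 10% rates and the 0.2 correlation are not in the protocol, so low power for complications overall is not established. At 10%, a halving would be well powered.

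**Conclusion.** The point holds as a mismatch between the stated hypothesis and the stated safety question. Superiority on complications has no basis in the rationale, and failing to show it would not support a claim that ISBCS is no worse. Under the assumed rates, equal observed results would still leave a relative excess of roughly 40% to 110% not excluded. That range depends on the assumed rates and, less strongly, on the correlation. For endophthalmitis the figures rest on the protocol's own rates: fewer than one case is expected per arm, and no reframing lets this trial settle the matter.

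The point goes no further. Large harm in common complications could be detected by the planned model if it is tested two-sided, and the sample size and primary analysis are not in error here. It concerns a secondary outcome and is worth correcting because it changes what may be concluded about safety.

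**What to change.** In Objectives, remove complications from the superiority list and add a safety objective: to estimate the difference in the incidence of complications, ISBCS minus DSBCS, with a two-sided 95% confidence interval. State that the conclusion rests on the upper limit, that is, on the largest excess not excluded, and not on a non-significant p-value. Make the sentence under Secondary outcomes agree; the mixed-effects logistic model can stay.

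Use the term non-inferiority for complications only if a justified margin is fixed in advance. The feasibility figures show that a narrow margin would leave the trial short of power at most of the assumed rates, so estimation is the safer choice.

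The cost is wording only: no change to sample size, data collection or the primary analysis. The small loss is that no superiority claim on complications could be made, and the rationale gives no reason to expect one.

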### Study design and setting

A multicenter non-inferiority randomized controlled clinical trial will be performed at outpatient ophthalmology clinics in one academic center (Maastricht University Medical Center (MUMC+)) and nine non-academic centers in the Netherlands (Zuyderland Medical Center, Heerlen; Canisius Wilhelmina Hospital, Nijmegen; Gelre Hospital, Zutphen; Deventer Hospital, Deventer; Elisabeth TweeSteden Hospital, Tilburg; Amphia Hospital, Breda; Medical Center Haaglanden, Den Haag; Medical Spectrum Twente, Enschede; Isala Clinic, Zwolle).

### Study population

All patients with bilateral cataracts undergoing expected uncomplicated bilateral cataract surgery using a standard phacoemulsification technique will qualify for inclusion in this study. The exclusion criteria are listed in Fig. 1.

**Fig. 1 Fig1:**
[figure not shown]
Exclusion criteria

### Study procedures

Visits are planned at baseline (preoperatively), and 1 week after first-eye surgery and 4 weeks after second-eye surgery. Patients will undergo study procedures as shown in Table 1. At 3 months after surgery, the occurrence of complications is derived from the patient record and patients will fill in the final questionnaires. Visual acuity will be measured by using the Early Treatment Diabetic Retinopathy Study (ETDRS) chart and measured refraction will be subjective (not automated).

**Table 1 Tab1:** Study procedures per follow-up time point

Assessment/ procedure	Visit					
	Preoperative	Surgery 1	1 week after surgery 1	Surgery 2 (if applicable)	4 weeks after surgery 2	3 months after surgery 1 (post/email)
Check for in−/exclusion criteria	X					
Informed Consent	X					
Medical history	X					
Check medication	X	X	X	X	X	X^a^
Ophthalmic examination	X		X		X	
Check adverse events		X	X	X	X	X^a^
Refraction	X		X		X	
CDVA	X		X		X	
NEI VFQ-25 questionnaire	X					X
Catquest-9SF questionnaire	X					X
EQ-5D-5L questionnaire	X		X		X	X
HUI-3 questionnaire	X		X		X	X
Cost questionnaire	X					X

^a^derived from the patient record and questionnaires

The intervention consists of bilateral cataract surgery by an experienced cataract surgeon. A standard phacoemulsification technique with intraocular lens implantation will be used. Surgery will be performed either during a single operating session (ISBCS) or during separate operating sessions with a minimum of 2 weeks apart (DSBCS), depending on randomisation. ISBCS will be performed in accordance with the “iSBCS General Principles for Excellence in ISBCS 2009”, treating both eyes as completely separate aseptic procedures in order to minimize the risk of bilateral endophthalmitis. For both ISBCS and DSBCS, intracameral antibiotics will be administered at the end of each operation. Topical antibiotics and anti-inflammatory drugs will be commenced postoperatively. After surgery, DSBCS patients will receive an eye patch and ISBCS patients will receive a transparent eye shield.

Patients can withdraw from the study at any time for any reason without any consequences. The investigator can decide to withdraw a patient from the study for urgent medical reasons. In case a patient withdraws from the study after randomization, the case is considered lost to follow-up, but will be included in the intention to treat analysis.

